#### Secondary questions

Does the new approach for implementation of integrated T2DM and periodontitis care:

lead to better periodontal health in response to dentist-initiated T2DM care?improve patients’ quality of life?lead to more risk-tailored utilization of care and medication?lend itself for practice implementation as anticipated? (process evaluation)provide good value-for-money?evoke specific provider payment preferences?

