## Materials & methods

### Endpoints

#### Primary endpoints

##### In general practitioner (GP) practices

HbA1c reduction among patients in the T2DM Disease Management Program (T2DM-DMP) who had not received periodontitis therapy within the past 12 months. Recorded by medical assistants at: T0 (recruitment); T1 (after 12 months); T2 (after max. 24 months). [primary data]

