##### Survey T1 (first follow-up)

The medical assistant in the general practice identifies all participating patients during a regular DMP-appointment. In the dental practice, the dental assistant identifies all participating patients during a regular appointment. Patients are asked to fill out another written questionnaire on their health and a potential periodontitis/T2DM diagnosis and therapy. Subjective health is once again assessed using the first question of the SF-36. To allow for a comparison with the patient’s subjective health at T0, question 2 of the SF-36 will be asked as well.

In the GP-study, the GP asks the patients about their potential periodontitis diagnosis and/or therapy. The primary endpoint measured during the regular DMP-appointment as well as the questionnaire data (including secondary endpoints) for T1 will be transferred to the research database by the medical assistant.

In the dentist study, the dentist in both control and intervention group asks the patients about their potential T2DM diagnosis and/or therapy. The current periodontal status and the periodontal services provided will, together with the questionnaire data, be transferred to the research database by the dental assistant.

The second, and final, follow-up survey takes place 6 to 12 months after T1, depending on when the patient was recruited for T0.

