#### Economic evaluation

A cost-cost-analysis will compare total costs for periodontitis- and diabetes-specific treatments in the intervention group with a representative control group. Simultaneously, a corresponding benefit-benefit-analysis will, in the context of a difference-in-differences analysis, analyze subjective health changes of study participants over the course of the study between intervention and control group.

In case of a positive or inconclusive result of these first analyses on the advantages of the intervention, the incremental cost-effectiveness-relation (ICER) of the intervention will be calculated in comparison to usual care and based on DMP and claims data as well as results from the main and process evaluation. Furthermore, there will be calculations on costs and effects of the transfer of the intervention to usual care. To calculate the ICER, differences in the costs will be compared with differences in health effects. Costs of usual care will be calculated from claims data [10]. Additional costs caused by the intervention will be estimated on the base of documented costs from the study and approximated personnel costs from the results of the process evaluation (time spent for the intervention multiplied with usual rates for personnel costs). All analyses will be performed using a validated R-environment with R version 4.2.2. or higher.

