## Expected use and insights of the study

The study will provide the following insights and have the following expected use for improved patient care within the study and healthcare more generally:

Quality of care: Improved care for T2DM and periodontitis is known to reduce morbidity and increase quality of life in patients. The participatory aspects of the new care approach will contribute to therapeutic success.Cost-efficiency: Periodontal care for T2DM patients are expected to yield a noticeable reduction of T2DM-associated care costs [9, 10, 31, 32]. Care costs per diabetes patient have been shown to be reduced by about 600 Euros within three years in response to periodontitis care [10].Elimination of care deficits: T2DM/periodontitis conditions that are currently diagnosed late or not at all will be detected earlier due to the targeted screening measures. Furthermore, we expect the intervention to lead to an ongoing improvement in oral health behavior as well as aftercare.Due to operationalization of structured and data-supported interdisciplinary care pathways, we expect DigIn2Perio to provide a valuable contribution to enhancing interprofessional and intersectoral collaboration.

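### The ICER is calculated only if the first cost and benefit comparisons are not negative, so the answer to the value-for-money question depends on the results

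*Protocol article*

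**What the plan says.** Under Secondary questions, the protocol article lists whether the approach will "provide good value-for-money". No condition is attached.

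The Economic evaluation part of Statistical analyses proceeds in two steps.

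- **First step, cost:** "A cost-cost-analysis will compare total costs for periodontitis- and diabetes-specific treatments in the intervention group with a representative control group".
- **First step, benefit:** a difference-in-differences comparison that will "analyze subjective health changes of study participants over the course of the study between intervention and control group".
- **Second step:** the ICER against usual care, to be calculated "In case of a positive or inconclusive result of these first analyses on the advantages of the intervention".

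The second step brings in items that the first does not name: documented costs of delivering the intervention, and personnel costs approximated from the process evaluation. The same paragraph announces calculations for a transfer to usual care. It does not say clearly whether these fall under the condition too.

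**The concern.** An ICER answers whether extra health is worth extra money. If it is produced only after a favourable or unclear first look, the set of results in which readers see it has been filtered by the results themselves. The decision-maker whom the article has in mind, who would consider the model for standard care under statutory insurance, would then lack the planned estimate in some of the cases where the decision is hardest.

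The matter is practical because of what the first step counts. Periodontitis and diabetes treatment are the services that the pathway is meant to increase. A pathway that works as designed can therefore look worse on the cost comparison while improving health. The text does not say how such a split result is to be classed.

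**Working it through.** There is no figure in the plan to reproduce for the condition itself. The check sets the passages side by side and then asks which results the rule settles.

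**1. Question against rule.** The value-for-money question is unconditional. The estimate that answers it is conditional on the first step being positive or unclear. By the wording, only a negative first step withholds it.

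**2. Direction of the cost comparison.** The inputs come from Sample size calculation.

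- *GP study.* At least 50% of patients are assumed to need periodontitis therapy, and 66% of these to use the referral: 0.50 × 0.66 = 0.33. The plan's own effect size relies on this share: 0.33 × 0.6 = 0.198, the 0.2 percentage points stated. So the plan expects about a third of intervention patients to take up dental care through the pathway. Periodontitis therapy is one of the two cost components in the first step.
- *Dentist study.* The assumed rate of new diabetes diagnoses is 0.05 under control and 0.10 under intervention. With 664 patients per group, (0.10 − 0.05) × 664 = 33.2, or about 33 additional diagnosed patients in the intervention group. Their diabetes treatment enters the other cost component.

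Against this stands the cited saving: "Care costs per diabetes patient have been shown to be reduced by about 600 Euros within three years in response to periodontitis care". It could offset the added cost in the GP study. It concerns periodontitis care in people with diabetes, and the article quotes no figure for savings from an earlier diabetes diagnosis. Unit costs of therapy are not given, so the sign of the cost difference cannot be derived. Higher cost is plausible but not established.

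**3. What the rule does with each result.**

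| Cost | Health | Verdict under the wording | Is a ratio needed? |
|---|---|---|---|
| lower | better | positive, ICER calculated | little, the pathway dominates |
| unclear | unclear | inconclusive, ICER calculated | yes |
| higher | better | not stated | most of all |
| lower | worse | not stated | yes |
| higher | worse | negative, ICER withheld | little, the pathway is dominated |

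The rule is clear where both comparisons agree or both are unclear. It does not settle the two trade-off rows, where a ratio or net benefit does its work. The row with higher cost and better health is the one that step 2 makes plausible. As the text stands, its class could be chosen after the results are known.

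**4. Does the first step already contain the answer?** Only in part. The cost comparison is described in terms of treatment costs. The costs of delivering the intervention are named only for the ICER. If the ICER is withheld, the full incremental cost need not appear anywhere.

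**The case against.** Several points on the other side are fair.

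- *The first step is unconditional.* Cost and health differences are reported in any case, and a result with higher cost and worse health already answers the question for the period covered. This stands for that one result. It does not cover the trade-off rows.
- *A split result may be meant to count as inconclusive.* The condition refers to both first-step analyses together, and nothing says that higher cost alone is negative. This stands, and is why the claim is that the ICER could be withheld, not that it will be.
- *The article is condensed.* Definitions of the verdicts and the economic time horizon may be in a fuller document. Their absence is therefore not the finding. The condition itself is a stated rule.

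A reader might go further and infer that short follow-up will make the first step negative, because the final survey falls 18 to 24 months after enrolment ("The second, and final, follow-up survey takes place 6 to 12 months after T1, depending on when the patient was recruited for T0", with T1 at 12 months) while the cited saving is for three years. The documents do not support this. A saving too small to show in that time would be inconclusive, and inconclusive results pass. No horizon is stated for the cost comparison. The three-year wording gives no time path. Even if the 600 Euros is assumed to accrue linearly, the saving per GP-study patient is 600 × 0.33 × 18/36 = 99 Euros to 600 × 0.33 × 24/36 = 132 Euros. Less the 30 Euros reimbursed per patient for the added services, that leaves 69 to 102 Euros, still favourable. Turning it negative needs a back-loaded saving or a therapy cost on top. The article gives neither, and does not say whether the 600 Euros is already net of therapy.

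**Conclusion.** The point holds in this form: the estimate that answers a listed secondary question is made conditional on the results, and a plausible result of an effective pathway, higher disease-specific cost with better health, could fall on the wrong side of the condition.

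It should be changed, but it is of moderate weight. It touches one secondary question and neither primary endpoint. No Euro magnitude is attached, since that would rest on a time path and therapy costs that the article does not give. The conclusion assumes only that the condition is applied as written and that the plan's own assumptions on referral uptake and new diagnoses are roughly right.

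It would be too strong to say that the value-for-money question will go unanswered, or that the length of follow-up is the cause.

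**What to change.** Delete the condition. State that incremental costs (including delivery costs), incremental effects, and the ICER or net benefit with its uncertainty will be reported whatever the first-step comparisons show. Net benefit is the easier quantity to present when the two differences point the same way as a dominance result or lie near zero. Label the result with the time horizon it covers, for costs and effects alike, and say that the transfer-to-usual-care calculations are also unconditional. A three-year scenario built on the cited saving is optional and should be marked as such.

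The cost is a few sentences in the analysis plan. The data are already to be collected or obtained. The one real consequence is that an unfavourable ICER would also have to be published.

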## Termination criteria

Individual termination criteria for practices and patients as well as overall termination criteria for the study are shown in Table 2:

**Table 2 Tab2:** Termination criteria for DigIn2Perio

Practices	Patients	Study
- Revocation of the consent to participate - Permanent loss of the infrastructure required to perform the study - Permanent closing - Relocation to a state outside of Baden-Württemberg or North Rhine-Westphalia - Transfer to an owner who is not willing to participate or who fulfills at least one exclusion criterion - Permanent loss of responsible assistant if no other person is willing/able to continue	- Revocation of the consent to participate - Death - Occurrence of at least one exclusion criterion in the course of the study - Permanent change of practice	- Permanent loss of the study funding - Loss of and/or actual incapacity to act at the study administration - Loss of project partners whose contributions are indispensable for the study, unless these contributions can be acquired elsewhere - Changes in legal regulations or the security situation that make it impossible to continue

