##### In dental practices

New T2DM diagnoses among periodontitis patients who had not been diagnosed with a diabetes condition before. Recorded by dental assistants at T1 (after 12 months). [primary data]

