#### Secondary endpoints

##### In GP practices

Utilization of periodontitis therapy (yes/no) [primary & claims data].T2DM medication (no medication, oral medication, insulin injections) [primary & claims data].Patients’ quality of life [primary data].

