##### Inclusion & exclusion criteria

Table 1 illustrates inclusion & exclusion criteria for practice personnel and patients alike in the main study.

**Table 1 Tab1:** Inclusion and exclusion criteria of the main study

	Practice & practice personnel	Patients
**Inclusion criteria**	- Legal age - Ability to consent	
	- Established, licensed physicians and assistants - Based in Baden-Wuerttemberg or North Rhine-Westphalia - Working computer system with internet connection - Patients physically visit the practice	- Insured with a statutory health insurer - GP-study: In T2DM-DMP in 4 of 5 past quarters - Dentist study: Need for systemic periodontitis therapy
**Exclusion criteria**	Persons who : - Live in a nursing home - Have a legal guardian - Are not of legal age - Are cognitively or linguistically incapable to participate	
	- Are not licensed as physician - Don’t practice in Baden-Württemberg or North Rhine-Westphalia	- Are not insured with a German statutory health insurer (or not entitled to care that exceeds basic health care coverage) - GP-study: a periodontitis therapy in the past 12 months - Not in the T2DM-DMP in 4 of 5 past quarters - Dentist study: Previously diagnosed with diabetes

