##### Sample size calculation

###### General practitioner study

Sample size calculation refers to the primary endpoint and is based on a t-test (α = 0.05; power = 0.8). We assume that HbA1c in the intervention group will decrease on average by 0.2%-points (standard deviation (sd) of 2.3) compared to the control group. The estimator results from the assumption that at least 50% of T2DM-patients have a need for periodontitis therapy [15, 20] and that they’re able to lower their HbA1c by 0.6%-points through therapy [8]. Out of these patients, an assumed 66% will use the referral to a dentist [21]. To account for cluster effects (patients clustered in practices), an intra-class-correlation of 0.03 and a cluster size of 10 patients per practice is assumed. For the control group calculated from claims data, we assume that it contains at least double the number of patients than the intervention group (allocation in a 2:1 ratio for control vs. intervention group). This results in a sample size of 1980 intervention patients (198 practices, 10 patients each) and 3960 control patients. With an assumed drop-out rate of 20%, there will be 2480 intervention patients (248 practices, 10 patients each) and 4950 control patients. Sample size calculation was performed using PASS v16.0.3.

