## Statistical analyses

### Analytic population

Primary statistical analysis is based on the full analysis set (FAS) following the intention-to-treat (ITT) principle and therefore being performed in accordance with current guidelines [26]. FAS includes all recruited patients (GP study) or those who were randomly assigned (dentist study) to a group, regardless of whether or not they actually participated in the intervention or dropped out of the study later on. This is the primary population for the evaluation of primary and secondary endpoints and study characteristics. To analyze the sensitivity of results, an analysis of the full dataset will be performed in addition. Drop-out and missing values will be accounted for by the intention-to-treat analyses. Missing values will be imputed.

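### Table 2 ends participation when an exclusion criterion arises during the study; as written this reaches dental patients with the primary endpoint and GP patients who receive periodontitis therapy, and contradicts the planned T1 and T2 data collection

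*Protocol article*

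**What the plan says.** - **Termination criteria, Table 2 (patients):** one reason for ending participation is "Occurrence of at least one exclusion criterion in the course of the study". No criterion is exempted.
- **Inclusion & exclusion criteria, Table 1 (patients):** the exclusions include "Dentist study: Previously diagnosed with diabetes" and "GP-study: a periodontitis therapy in the past 12 months".
- **Primary endpoints, In dental practices:** the endpoint is "New T2DM diagnoses among periodontitis patients who had not been diagnosed with a diabetes condition before", recorded at T1.
- **Secondary endpoints:** use of periodontitis therapy is an endpoint in the GP study. T2DM medication and use of T2DM care are endpoints in the dentist study.
- **Sample size calculation, General practitioner study:** the assumed effect comes entirely from periodontitis therapy. It assumes that "at least 50% of T2DM-patients have a need for periodontitis therapy", that 66% of these use the referral, and that "they’re able to lower their HbA1c by 0.6%-points through therapy".
- **Survey T1 and Survey T2:** participating patients are asked about a diagnosis and therapy of the other condition at both visits.
- **Analytic population:** the full analysis set (FAS) keeps patients "regardless of whether or not they actually participated in the intervention or dropped out of the study later on". Missing primary outcomes are multiply imputed using age, sex, insurance status and residential area (Statistical hypotheses and analyses, both studies).

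**The concern.** The two study-specific exclusions name the events that the intervention is meant to produce. A practice that follows Table 2 literally would end follow-up of a dental patient when diabetes is diagnosed, and of a GP patient when periodontitis is treated. If this happens before T1, whether the T1 value is missing depends on the outcome itself (dentist study) or on the therapy through which the effect is assumed to arise (GP study).

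None of the listed imputation variables carries information on the diagnosis or the therapy. Imputed values would therefore resemble those of patients without the event or without treatment, and both primary effects would be pulled toward zero.

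Loss may also differ between groups. Under T0 in dental practices, only high-risk intervention patients are asked between visits what the GP did, so their diagnoses are more likely to be known before T1. In the GP study the controls come from claims and DMP data, and the article does not say that the rule is mirrored there.

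**Working it through.** **1. Does the rule reach these patients?** Both criteria look back in time, but Table 2 applies the exclusions to follow-up. The GP criterion is a 12-month window. T1 falls 12 months after T0, so at T1 the window covers the whole period since enrolment, and any therapy in that period meets it. The T1, T2 and secondary endpoint sections assume that these patients are still being followed. The passages conflict.

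**2. The plan's own sample sizes reproduce** (two-sided 5%, power 80%).
- Dental, unpooled Z-test: (1.960 + 0.842)² × (0.10×0.90 + 0.05×0.95) / 0.05² = 431.7 per group. The design effect is 1 + 7×0.03 = 1.21, giving 522.3, or 66 practices of 8 = 528. Then 528/0.8 = 660, or 83 practices = 664.
- GP, difference 0.2, SD 2.3, 2:1 allocation: 3115 controls and 1557.5 intervention patients. The design effect is 1 + 9×0.03 = 1.27, giving 3956 and 1978, stated as 3960 and 1980. Dividing by 0.8 gives 4950 and 2475, the latter rounded up to 248 practices = 2480.

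**3. Upper bound on patients reached.**
- Dental: 0.10×664 = 66 intervention and 0.05×664 = 33 control patients.
- GP: 0.50×0.66 = 0.33, and 0.33×2480 = 818, if every referral user is treated before T1. These patients carry the whole assumed effect: 0.33×0.6 = 0.198, the stated 0.2.

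**4. Partial application.** Let f be the share of these patients terminated before T1 is recorded. The article gives no value, so f is an assumption. The analysis is of observed patients.

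Dental: the observed rate is p(1−f)/(1−pf), with effective n held at 528/1.21 = 436 per group.

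| f | Intervention | Control | Power |
|---|---|---|---|
| 0 | 10.0% | 5.0% | 80% |
| 25%, both arms | 7.7% | 3.8% | 70% |
| 50%, both arms | 5.3% | 2.6% | 54% |
| 50%, intervention arm only | 5.3% | 5.0% | effect nearly gone |

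GP: the treated share among observed patients is 0.33(1−f)/(1−0.33f), the effect is 0.6 times that share, and the intervention n is 1980(1−0.33f). The standard error is 2.3×√(1.27/n + 1.27/3960), with controls unaffected.

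| f | Effect (%-points) | Intervention n | Power |
|---|---|---|---|
| 0 | 0.198 | 1980 | 79% |
| 25% | 0.162 | 1817 | 60% |
| 50% | 0.119 | 1653 | 35% |

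**5. T2.** A patient terminated at or after T1 still loses T2. In the GP study T2 is meant to show whether the HbA1c reduction lasts; in both studies it gives the long-term picture of the secondary endpoints.

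**The case against.** The strongest reply is that the two criteria were meant for entry only. A diagnosis after T0 is the endpoint and not a previous diagnosis, and the endpoint definitions use the same look-back terms to describe the population at enrolment. Table 2 would still have content, because nursing-home residence, guardianship, cognitive incapacity or leaving the DMP can arise later. The follow-up sections describe these patients being seen at T1 and T2. This is a plausible account of the intent, especially for the diabetes criterion. It fits poorly with Table 2's explicit extension to the course of the study and with the 12-month GP window. The follow-up sections show that the text conflicts; they do not settle which part a practice would follow.

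The reply does limit the size of the problem. A reader might infer that every dental event is lost, that 818 GP patients disappear, and that the GP effect falls to about zero. The article does not support this. It would require every event to be known to the practice, acted on and left unrecorded before T1. A diagnosis first disclosed at T1 can still be entered. No questioning of dental controls between visits is described. The 66% is referral use, not treatment. T1 HbA1c is taken at a regular DMP appointment. Table 2 also does not say that information already known is discarded.

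A reader might also infer that these patients leave the analysis, in breach of intention-to-treat. They do not: the FAS keeps drop-outs. The problem is outcome-related missing data.

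**Conclusion.** The point holds as a contradiction between Table 2, read with Table 1, and the T1, T2 and secondary endpoint sections, with consequences for both primary endpoints if Table 2 is followed. Where it is applied before T1, data may be missing because of the outcome or the mediating therapy. The planned imputation cannot correct this, and the effects would tend toward zero.

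The counts of 66, 33 and 818 are ceilings on the plan's own rates. The power losses depend on an assumed 25% to 50% of affected patients being terminated before T1, on an observed-case analysis and, for the GP study, on unaffected controls. The actual share cannot be obtained from the article. The case for correcting the text does not depend on it: any share above zero does harm, and the correction is small.

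**What to change.** Reconcile Table 1, Table 2 and the T1 and T2 sections. Amend Table 2 so that, for study participation and data collection, previous diabetes (dentist study) and recent periodontitis therapy (GP study) are checked at T0 only. State that patients who meet either criterion after T0 keep their T1 and T2 data collection and enter the FAS with observed values. If the rule has already been applied, retrieve T1 data where routine records hold them.

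The cost is a short amendment, a notice to practices and possibly some data retrieval. The stated sample sizes stand, and nothing in patient care changes.
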